### Outcomes

2.6

The indicators of intestinal flora, IR, blood glucose, blood lipid, BMI, anxiety, and sleep status will be collected before, 3, and 6 months after the intervention. The incidence of T2DM will be observed after 1 year follow-up after the intervention.

All indicators will be tested in the Hospital of Chengdu University of traditional Chinese medicine.

#### Primary outcomes

2.6.1

1.Intestinal floraThe sterile stool box will be distributed to PDM patients, and the patients were instructed to collect 5 to 10 g stool for the first time in the morning. Sterile feces will be detected by 16S fragment high-throughput sequencing. Through the relevant results of intestinal flora, the number and species of intestinal flora in patients with PDM before and after intervention will be obtained, and the results will be analyzed and compared.2.IR indexFasting venous blood samples will be collected from all participants. Fasting blood glucose (FBG) and fasting insulin (FINS) will be measured by automatic biochemical analyzer (model: AU5800) of Beckman Coulter company. The insulin resistance index (HOMO-IR) will be calculated as an auxiliary measure of insulin sensitivity (HOMO-IR = FBG × FINS/22.5).

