Baduanjin is a moderate intensity aerobic exercise. Baduanjin is based on the theory of Traditional Chinese medicine (TCM) and has a history of more than 1000 years. Baduanjin is very popular in China. Similar to the traditional Taijiquan, Baduanjin has the characteristics of slow movement and relaxation. It is easy to learn and practice and is less likely to cause harm. A set of 8 section brocade qigong practice method, in addition to the starting and stopping movements, also includes 8 movements, each of which is repeated 4 to 8 times. It usually takes about 15 to 20 minutes to complete. Some studies found that through Baduanjin, the blood glucose and blood lipid of PDM patients were significantly improved.^[20]^ Sun Hongmei has proved that Baduanjin has a positive effect on the intestinal flora of the elderly and significantly improves the intestinal microecological balance, which is mainly manifested in the increase of beneficial bacteria Bifidobacterium and Lactobacillus, and the decrease of conditional pathogenic bacteria and harmful bacteria such as Enterobacter, Fusobacterium, and Enterococcus.^[20]^ The fitness effect of Baduanjin was confirmed from the view of microbiology. However, the effect of Baduanjin on intestinal flora of patients with PDM and its correlation with insulin resistance (IR) need to be further studied.

Intestinal flora is a kind of microflora which is located in the human intestinal tract. The intestinal microflora is closely related to the energy metabolism of human body.^[21–23]^ Microbiological studies showed that there were significant differences in the number and species of intestinal flora between diabetes mellitus (DM) patients and normal people.^[24,25]^ Metabolic products produced by microorganisms and host regulation are the key factors affecting IR.^[26]^ The beneficial bacteria in the first gut can correct IR by regulating lipid metabolism of the host. Beneficial bacteria can decompose food components that cannot be digested by the host and convert them into short chain fatty acids. Intestinal probiotics can improve IR by reducing the occurrence of inflammatory reaction.^[27–29]^ In addition, intestinal probiotics can correct impaired glucose tolerance by regulating oxidative stress factors.^[30,31]^ Intestinal flora is closely related to the occurrence and development of T2DM-IR.

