We designed a randomized clinical trial to study the effect of Baduanjin on prediabetic patients. The purpose of this study is to determine whether Baduanjin can change the type and quantity of intestinal flora in patients with prediabetes mellitus so as to improve the IR state, and ultimately achieve the recovery of impaired glucose regulation to normal glucose regulation in patients with PDM, effectively delay or even prevent the occurrence of T2DM.

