### Sample size estimation

2.5

Our preliminary study reported that the standard deviation of intestinal microflora in patients with prediabetes was 6.28 CFU/g. At a significant level of 0.05, 80% power was required to detect blood glucose. The average difference between the 2 groups was 5.1 cfu/g. The formula for calculating the sample size is as follows: 

Therefore, we calculated at least 32 sample sizes for each study group, and expected to lose 20% in the future. After calculation, a total of 80 people were admitted.

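### The purpose and sample size treat gut flora as an absolute amount, but the only assay described, 16S sequencing, gives relative composition and diversity, so a conclusion on bacterial quantity would be unsupported

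*Protocol article*

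**What the plan says.** Three places in the protocol article bear on what is meant by flora.

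- **Purpose (end of the Introduction).** The trial is to determine "whether Baduanjin can change the type and quantity of intestinal flora in patients with prediabetes mellitus".
- **Sample size (section 2.5).** The inputs are absolute: "the standard deviation of intestinal microflora in patients with prediabetes was 6.28 CFU/g" and "The average difference between the 2 groups was 5.1 cfu/g". The sentence between them names another variable: "At a significant level of 0.05, 80% power was required to detect blood glucose".
- **Primary outcome (section 2.6.1).** The assay is named: "Sterile feces will be detected by 16S fragment high-throughput sequencing". From its results, "the number and species of intestinal flora in patients with PDM before and after intervention will be obtained".

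No culture, total-load measurement, quantitative PCR or spike-in is described. Section 2.9 plans a two-sample t test for normally distributed measurements, a Wilcoxon Mann–Whitney test otherwise, and a chi-square test for counts, all two-sided at 0.05. The insulin resistance index is listed as a second primary outcome.

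**The concern.** The purpose and the sample size ask about an amount of bacteria. The instrument reports proportions. In 16S amplicon sequencing, the number of reads per sample is governed by sequencing depth rather than by how many bacteria are in the stool. The taxon results are therefore shares that sum to 1. This is a general property of the method.

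Two things follow. First, a statement at the end of the trial that Baduanjin changed the quantity of flora would have no measurement behind it. Second, because shares must sum to 1, a rise in one taxon pushes the other shares down. A taxon whose amount did not change can then appear to fall, and the tests in section 2.9, applied to a single share, would not reveal this.

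The sample-size basis has the same problem: a standard deviation and a difference in CFU/g do not describe the variability of a 16S result.

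**Working it through.** **1. The plan's own figure.** Inputs from section 2.5: SD 6.28 CFU/g, difference 5.1 CFU/g, alpha 0.05, power 80%. Section 2.9 makes the test two-sided. With equal groups,

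n per group = 2 × (z₀.₉₇₅ + z_power)² × (SD/difference)²

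- (6.28/5.1)² = 1.516
- 80% power: 2 × (1.960 + 0.842)² × 1.516 = 23.8, so 24 per group
- 90% power: 2 × (1.960 + 1.282)² × 1.516 = 31.9, so 32 per group

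The stated 32 per group matches 90% power, not the stated 80%. The dropout step reproduces: 32/(1 − 0.20) = 40 per group, 80 in total. The power mismatch is a separate matter. What counts here is that the calculation rests entirely on the ratio 5.1/6.28 = 0.81, and both numbers are absolute counts per gram. The article gives no SD or difference for a diversity index, a share or a log-ratio. The power for a 16S endpoint therefore cannot be computed from it in either direction.

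**2. Target against instrument.**

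| Place | What it refers to | Scale |
|---|---|---|
| Introduction, purpose | type and quantity | *type* relative, *quantity* absolute |
| Section 2.5 | CFU/g | absolute |
| Section 2.6.1, assay | 16S sequencing | relative |
| Section 2.6.1, result | number and species | *species* relative, *number* ambiguous |

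The absolute entries have no matching measurement.

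**3. The forced fall.** Let one taxon start at share p and double in amount, with every other taxon unchanged. The total becomes 1 + p, so

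- new share of that taxon = 2p/(1 + p)
- every other share is multiplied by 1/(1 + p), a relative fall of p/(1 + p)

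| Assumed p | New share | Apparent fall of every other taxon |
|---|---|---|
| 10% | 0.20/1.10 = 18.2% | 0.10/1.10 = 9.1% |
| 20% | 0.40/1.20 = 33.3% | 0.20/1.20 = 16.7% |
| 30% | 0.60/1.30 = 46.2% | 0.30/1.30 = 23.1% |

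The starting shares, the doubling and the constancy of the rest are all assumptions.

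**4. What a t test would do with it.** The settings here are also assumed: five equally abundant taxa, independent log-normal amounts, one taxon doubled in the experimental arm, and a two-sided t test at 0.05 on the share of an unchanged taxon, with 3,000 simulated trials per setting.

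| Log-SD | 32 per arm | 40 per arm |
|---|---|---|
| 0.3 | 70% | 81% |
| 0.5 | 32% | 38% |
| 0.8 | 15% | 17% |

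These are the percentages of trials in which the unchanged taxon is declared different. Tested on its true (log) amount, the rate stays near 5%. The spread from 15% to 81% shows how strongly the result depends on inputs that the article does not give.

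**5. What a log-ratio does and does not solve.** The total cancels in the ratio of two taxa, so two unchanged taxa keep their ratio. But a ratio that doubles because the numerator doubled (2/1) equals one that doubles because the denominator halved (1/0.5). A log-ratio shows a shift in balance, not which side moved.

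**The case against.** The strongest reply is that *number* in section 2.6.1 may mean the number of taxa, that is, richness. 16S can estimate richness, and on that reading the primary-outcome section contains no error. This stands for that one word. It does not remove CFU/g from section 2.5, and it does not give *quantity* in the purpose a clear meaning other than amount.

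A second reply is that this is a condensed article, and a total-load step could sit in a full protocol that is not shown. That also stands, so the point is limited to the assay as described. It does not disappear, because the article names the assay and says what will be obtained from it.

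A reader might go further and infer that the trial expects beneficial bacteria to rise and harmful ones to fall, and so is set to report a false fall in harmful bacteria. The documents do not support this. The Introduction gives "the increase of beneficial bacteria Bifidobacterium and Lactobacillus, and the decrease of conditional pathogenic bacteria and harmful bacteria" as a result of an earlier study in the elderly, and then says the effect in prediabetes needs further study. Neither the purpose nor section 2.6.1 sets a direction for any genus. The forced fall is also uniform across all other taxa, unlike a selective fall in named genera.

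**Conclusion.** The point holds in a limited form. The purpose and the sample size refer to an absolute amount, the only flora assay described yields relative composition and diversity, and a conclusion on absolute bacterial quantity would therefore be unsupported. This rests on the article describing the assay completely; a total-load measurement elsewhere would remove it.

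The risk that a share falls only because another rose is real in kind, but its size is not known. The 9.1% to 23.1% range and the simulated rates illustrate the mechanism under assumed inputs and are not estimates for this trial.

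It would be too strong to say that the flora primary cannot be answered at all. Type, species, composition and diversity remain within reach of the assay, and the insulin resistance primary is untouched. The wording should be corrected before the flora results are analysed; the design itself can stand.

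**What to change.** - **Introduction (purpose) and section 2.6.1.** Restate the flora outcome as relative composition or diversity, and name one between-arm measure at month 6. Either choose an alpha-diversity index (richness, if that is what *number* means), analysed on its own scale, or a log-ratio of prespecified genera, interpreted only as a shift in their balance.
- **Same places.** State that changes in absolute bacterial number will not be concluded.
- **Section 2.5.** Stop presenting the CFU/g inputs as the basis for the 16S endpoint. Restate the basis on the chosen scale, giving the SD and difference used and their source.

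Cost: wording, an analysis of data already being generated, and a new sample-size justification. No extra samples are needed. The downside is that the trial gives up its claim about absolute quantity, and the stated power for the flora primary may change once it is worked out on the new scale.

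If the sponsor wants to keep quantity in the purpose, the alternative is to describe a total bacterial load measurement (for example quantitative PCR or a spike-in) on the same stool samples, at the cost of an added assay. Section 2.5 would still need to match the endpoint so defined.

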#### Secondary outcomes

2.6.2

1.Fasting blood glucose and 2 hours postprandial blood glucose;2.The concentrations of triglyceride (TG), total cholesterol (TC), high density lipoprotein cholesterol (HDL-C), low density lipoprotein cholesterol (LDL-C);3.Changes in body weight (kilogram) and body mass index (kilogram per meter square);4.Waist to hip ratio;5.Anxiety was assessed by Hamilton Anxiety Scale (HAMA), that scale includes 14 items;6.Sleep status assessment: Pittsburgh sleep quality index (PSQI), that scale consists of 18 self-rated items.

### Discontinuation and withdrawal

2.7

1.Those who are not willing to continue to cooperate with the test and ask to withdraw after joining the group;2.Poor compliance and failure to complete the intervention as required;3.The total training times are less than 70% or each training is lower than the required time and intensity.

### Data management

2.8

Data entry will be conducted by clerks trained in research data entry. All participants will be assigned a participant number, and all data will be stored in a server that only research team members can access. A range check is performed on the data value.

### Data analysis

2.9

In order to evaluate the effect of Baduanjin intervention and conventional lifestyle intervention, the results will be compared. Spss21.0 will be used for statistical analysis of all the data. The statistical analysis will take bilateral test, and take α = 0.05 as the test level. If the measurement data conform to the normal distribution, the description of 

 is adopted. If it does not meet the normal distribution, it is described by the median and quartile interval. In the result analysis, if the data conform to the normal distribution, the *t* test of 2 independent samples is used for statistical inference. The Wilcoxon Mann–Whitney rank sum test is used to infer if the distribution does not conform to the normal distribution. The counting data were analyzed by person chi square test.

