### Randomization and blinding

2.3

The patients who passed the qualification assessment will randomly divide the random participants into the Baduanjin group or the routine lifestyle intervention group, and use computer-generated random numbers (FileMarker Pro) for stratification. Data analysts and key outcome assessors will blindly assign treatment assignments. However, some researchers need to conduct the Baduanjin teaching campaign and supervise the experiment, and they will know the group they are assigned to.

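### Continuous outcomes are compared by two-sample tests with no baseline adjustment, although baseline values are collected, so precision is lost that could be had at almost no cost

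*Protocol article*

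**What the plan says.** Section 2.9 (Data analysis) sets two-sided testing at 0.05. For continuous data that look normal, the t "test of 2 independent samples is used for statistical inference"; otherwise the Wilcoxon-Mann-Whitney test applies. No baseline covariate, stratification factor or repeated-measures model is named. The section also does not say whether the tests are run on follow-up values or on changes from baseline.

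Section 2.6 (Outcomes) lists flora, insulin resistance, glucose, lipids, BMI, anxiety and sleep as data that "will be collected before, 3, and 6 months after the intervention". Waist-to-hip ratio is absent from that sentence, but the Discussion counts it among the changes to be measured. The exception is the incidence of type 2 diabetes at 1 year, which has no baseline value because people with diagnosed diabetes are excluded.

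Section 2.3 says the trial will "use computer-generated random numbers (FileMarker Pro) for stratification" but names no stratification factor. Section 2.5 bases the sample size on flora: "standard deviation of intestinal microflora in patients with prediabetes was 6.28 CFU/g" and "The average difference between the 2 groups was 5.1 cfu/g".

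**The concern.** A patient's baseline value often predicts the same patient's later value. A two-sample test on follow-up values leaves that predictable part in the error term, so confidence intervals are wider than the data require. A chance difference between arms at baseline also goes uncorrected into the result. A test on changes does use the baseline value, but subtracts all of it whatever the correlation. When the correlation is low, this adds noise.

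The trial is small: 80 randomised, with 32 per arm expected after 20% loss. Section 2.6.1 names two primary outcomes, flora and HOMA-IR (printed there as HOMO-IR), but section 2.5 takes its standard deviation and difference from flora alone. For HOMA-IR and the secondary outcomes the article offers no assurance of adequate power. A separate test at each visit also makes no use, at 6 months, of a participant seen at month 3 and then lost.

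**Working it through.** **Inputs from the article.** SD 6.28 and difference 5.1 (section 2.5); two-sided alpha 0.05 ("At a significant level of 0.05" in section 2.5, "The statistical analysis will take bilateral test" in section 2.9); power 80% ("80% power was required to detect blood glucose"); 20% loss; equal arms.

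**Assumptions.** The article gives no baseline-to-follow-up correlation r, so I use 0.3, 0.5 and 0.7. I take 6.28 as the SD of values at one visit, equal at baseline and follow-up.

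**1. The article's own sample size.** n per arm = 2(z₁₋α/₂ + z_power)² × SD²/difference².
- At 80% power: 2 × (1.960 + 0.842)² × 6.28²/5.1² = 23.8, so 24 (exact t: 25).
- At 90% power: 2 × (1.960 + 1.282)² × 6.28²/5.1² = 31.9, so 32 (exact t: 33).

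The stated 32 is therefore the 90% figure, not the 80% figure. The loss step reproduces: 32/(1 − 0.20) = 40 per arm, 80 in total. The mismatch on power is a separate matter. Here it means only that flora has more power than stated.

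**2. ANCOVA against a t test on follow-up values.** The standard error ratio is √(1 − r²), and 32 per arm are worth 32/(1 − r²).
- r = 0.3: √0.91 = 0.954; 32/0.91 = 35.2
- r = 0.5: √0.75 = 0.866; 32/0.75 = 42.7
- r = 0.7: √0.51 = 0.714; 32/0.51 = 62.7
- r = 0: ratio 1, no gain

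**3. ANCOVA against a t test on changes.** The SD of a change is SD × √(2(1 − r)). The variance ratio is (1 − r²)/(2(1 − r)) = (1 + r)/2.
- r = 0.3: 32/0.65 = 49.2
- r = 0.5: 32/0.75 = 42.7
- r = 0.7: 32/0.85 = 37.6

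ANCOVA is the more precise in each case. Which reading of section 2.9 costs more depends on r.

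**4. Power for flora at 32 per arm.** The standardised difference is 5.1/6.28 = 0.81 SD. Power is from the noncentral t. The smallest difference detectable with 80% power is (1.960 + 0.842) × SD × √(1 − r²) × √(2/32).

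| Analysis | Power | Detectable difference |
|---|---|---|
| t test on follow-up values | 89.2% | 4.40 |
| ANCOVA, r = 0.3 | 91.8% | 4.20 |
| ANCOVA, r = 0.5 | 95.8% | 3.81 |
| ANCOVA, r = 0.7 | 99.4% | 3.14 |

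By the normal approximation, a t test on changes has 78.4%, 90.1% and 98.7% power at the three correlations, against 92.6%, 96.3% and 99.5% for ANCOVA.

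**5. A smaller effect, for illustration.** An effect of 0.6 SD is my assumption and appears nowhere in the article. At 32 per arm the t test on follow-up values has 65.6% power. ANCOVA has 69.7%, 77.9% and 91.1% at r = 0.3, 0.5 and 0.7.

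**The case against.** The strongest reply is that an unadjusted two-sample test is a legitimate analysis of a randomised trial, and that a condensed article may leave covariates to a fuller document. The first part stands: the test is valid, and nothing in section 2.9 is false. The second part does not remove the point, because section 2.9 names the inferential test. The comment is on that stated choice.

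It is also fair that flora, the only outcome with a sample-size basis, already has about 89% power unadjusted, and that at low r adjustment gains little. Both stand and limit the size of the point.

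A reader might infer more than the article supports:

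- **That baseline imbalance necessarily passes into the result.** This applies to a test on follow-up values. The article may mean changes: section 2.6.1 speaks of flora before and after intervention, and section 2.6.2 lists changes in body weight.
- **That ignoring the strata makes the standard error too large.** This holds only if the factors predict outcome. None is named, so the cost cannot be judged.
- **That HOMA-IR will be skewed and left without an effect estimate.** Skewness is plausible for a product of glucose and insulin, but the article has no data on it. A Hodges-Lehmann shift can accompany a rank-sum test. The ratios above compare ANCOVA with a t test and do not measure the loss for a rank-sum test.
- **That every outcome has a baseline value.** One-year diabetes incidence does not.

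**Conclusion.** The point holds as one of efficiency, not validity. For the listed continuous outcomes, the stated tests are less precise than a baseline-adjusted comparison unless the correlation is near 0 (for follow-up values) or near 1 (for changes). Over assumed correlations of 0.3 to 0.7, adjustment makes 32 per arm worth about 35 to 63 if follow-up values would otherwise be tested, or about 49 down to 38 if changes would be. These figures rest on the assumed r, equal variances at the two visits and approximate normality.

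The article does not support calling the trial underpowered for flora for want of adjustment: power there moves from about 89% to 92%, 96% or 99%. The practical benefit lies with HOMA-IR and the secondary outcomes, where the effect may be smaller than 0.81 SD and no calculation protects the comparison. The direction of the gain is well established; its size in this trial is not. The change is worth making because it uses data already planned.

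**What to change.** In section 2.9, make the primary analysis of each continuous outcome a baseline-adjusted comparison at 6 months. The preferred form is a linear mixed model for the 3- and 6-month values with treatment, visit, treatment-by-visit and baseline value, so that participants lost after month 3 still contribute. ANCOVA at 6 months is simpler and gives the baseline gain, but does not recover those participants.

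State the stratification factors actually used in the randomisation and include them in the model. Analyse HOMA-IR on the log scale if it is skewed. Report the adjusted difference, or the ratio for a logged outcome, with its 95% confidence interval. Keep the t and rank-sum tests as sensitivity analyses, and say whether they are run on follow-up values or changes. One-year diabetes incidence stays outside this model.

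The cost is a few degrees of freedom and a change of wording, including naming the strata. No new data are needed, and the SPSS version already named can fit these models.
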